**Figure 1 F1:**
[figure not shown]
Overview of study procedure

### Randomization

Randomization will be performed to determine whether the patient will receive usual care (n = 70) or usual care plus the decision aid (n = 100). To accomplish this, a computer generated randomization list is prepared that is stratified by hospital, using a block size of 3. Each participating hospital will receive three sets of sealed envelopes, related to colorectal, breast, and ovarian cancer patients. When disease progression is diagnosed by the oncologist, a nurse will perform the randomization by opening the appropriate envelope.

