**Methods/Design:**

This study is a randomized controlled trial of patients with advanced colorectal, breast, or ovarian cancer who have started treatment with first-line palliative chemotherapy. The trial will consist of 100 patients in the decision aid group and 70 patients in the usual care group. To collect complete data of 170 patients, 246 patients will be approached for the study. Patients will complete a baseline questionnaire on sociodemographic data, well-being measures, and psychological measures, believed to predict information desire. The medical oncologist will judge the patient's information desire. After disease progression is diagnosed, the medical oncologist offers the choice between second-line palliative chemotherapy plus best supportive care (BSC) and BSC alone. Randomization will take place to determine whether patients will receive usual care (n = 70) or usual care and the decision aid (n = 100). The aid offers information about the potential risks and benefits of both treatment options, in terms of adverse events, tumour response, and survival. Patients decide for each item whether they desire the information or not. Two follow-up questionnaires will evaluate the effect of the decision aid.

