## Methods/Design

### Patients

In 11 hospitals in the Netherlands, all patients with advanced colorectal, breast, or ovarian cancer who have started treatment with first-line palliative chemotherapy and upon disease progression will be faced by the choice regarding second-line palliative chemotherapy will be included. Exclusion criteria are labile personality structure, as assessed by the physicians, a Karnofsky performance score lower than 60, and insufficient knowledge of the Dutch language. The study has been approved by the research ethics committees of all participating hospitals.

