### Sample size calculation

Our primary research question is whether or not patients want to be informed. For study question 1a, about 100 patients in the intervention group will suffice to estimate an assumed desire rate for prognostic information of 80% with 95% confidence interval from 71% to 87%. For study question 1b, regarding factors that determine information desire, again about 100 patients will suffice to detect a weak correlation of 0.28 between a predictor and information desire, with α = 0.05 and a power equal to 0.82. For question 2, dealing with the ability of the medical oncologist to judge whether or not the patient wants this information, the same analysis applies as for study question 1b. For study question 3, which addresses the effect of the introduction of decision support compared to usual care on patient well-being, the intervention group is compared to the usual care group. Because one of the main concerns of physicians is that information on prognosis provokes anxiety, anxiety is used as the main outcome measure. We assume that the HADS anxiety difference between the two groups at t3 is equal to 2.2, and the correlation between the measurements at t1 and t3 equals 0.72. The standard deviation in each cell is about 6, corresponding to a medium sized effect size of 0.36. With α = 0.05, and 70 patients in each group, the power to detect the assumed effect is equal to 0.81. In conclusion, 100 patients in the intervention group and 70 patients in the usual care group suffice to answer the above research questions. Assuming that 30% of the patients refuse to give informed consent, and that 1% of patients has died at t3, 246 patients will have to be approached.

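### Blocks of 3, read as fixed 2:1 blocks, give about 113 decision-aid and 57 usual-care patients out of 170, not the stated 100 and 70; no stated power or precision is lost

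*Protocol article*

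**What the plan says.** The Randomization section names the two arms and their sizes as "usual care (n = 70) or usual care plus the decision aid (n = 100"). To achieve this, the computer list is "stratified by hospital, using a block size of 3". The same section adds: "Each participating hospital will receive three sets of sealed envelopes, related to colorectal, breast, and ovarian cancer patients". The Patients section sets the trial "In 11 hospitals in the Netherlands". The article does not state how many of the three places in a block go to each arm.

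The same arm sizes appear in the Methods/Design part of the abstract, which also gives the totals: "To collect complete data of 170 patients, 246 patients will be approached for the study". The Sample size calculation ends with the statement that "100 patients in the intervention group and 70 patients in the usual care group suffice to answer the above research questions".

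The figures behind that conclusion differ by question. Questions 1a, 1b and 2 use about 100 patients in the intervention group only; question 1a, for example, is sized to "estimate an assumed desire rate for prognostic information of 80% with 95% confidence interval from 71% to 87"%. The power of 0.81 for question 3 (HADS anxiety at t3) is computed with 70 patients in each group.

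**The concern.** The target ratio is 100:70, or about 1.43 to 1. Two arms cannot share a block of three in that ratio. With one fixed composition, the only splits that use both arms are 2:1 and 1:2. The list is presented as the means of reaching 100 and 70, so the section prescribes a method that, on its natural reading, does not give the result it names.

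Staff who follow the list will not end with both stated arm sizes at 170 patients. A reader who compares the final arms with the plan would see a gap of about 13 in usual care and could not tell whether it came from the design or from a failure in allocation. This matters more than usual here, because the Discussion relies on comparing allocations with the predetermined sequence to detect subversion of the envelopes. It also has to be settled whether the smaller usual-care arm weakens any stated calculation.

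**Working it through.** **Inputs.** From Randomization: block size 3, stratified by hospital, three envelope sets per hospital, arms of 100 and 70. From Patients: 11 hospitals, hence up to 11 × 3 = 33 sequences. From Sample size calculation: difference 2.2, SD about 6, t1–t3 correlation 0.72, α = 0.05 (two-sided assumed, as the article does not say), 70 per group, power 0.81; correlation 0.28 with power 0.82; rate 80% with interval 71% to 87%; refusal 30%, death 1%.

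**1. The plan's own figures.**
- Approached: 170 / (0.70 × 0.99) = 245.3, rounded up to 246. Reproduced.
- Question 1a: exact 95% interval for 80/100 is 70.8% to 87.3%. Reproduced.
- Question 1b: Fisher z with n = 100 and r = 0.28 gives power 0.81, against 0.82 stated. Reproduced closely.
- Question 3: the SD of a change score is 6 × √(2 × (1 − 0.72)) = 4.49. The standard error at 70:70 is 4.49 × √(1/70 + 1/70) = 0.759, and 2.2 / 0.759 = 2.90. Power is Φ(2.90 − 1.96) = 0.83 (0.82 with the noncentral t), against 0.81 stated. The alternatives are further off: the raw SD of 6 gives 0.58, and the ANCOVA SD of 6 × √(1 − 0.72²) = 4.16 gives 0.88 (0.87 by t).

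**2. What blocks of 3 deliver.** At 2:1, 170 × 2/3 = 113.3 decision aid and 170/3 = 56.7 usual care. The shortfall against 70 is about 13.

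Unfinished last blocks could in principle shift this, so 170 patients were simulated over 11 and over 33 sequences, with even and with uneven recruitment, 40,000 runs per setting. The usual-care count averaged 56.7, with 99% ranges of 54–60 (11 sequences) and 51–62 (33 sequences, even recruitment). The largest count in any run was 65; none reached 70.

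**3. What happens to power and precision at 113:57.**
- Question 1a: 90/113 gives an exact interval of 71.0% to 86.6%, slightly narrower than planned.
- Question 1b: power at n = 113 is 0.85, against 0.81 by the same method at n = 100.
- Question 3: the equivalent equal group size is 2 × 113 × 57 / 170 = 75.8, which is more than 70. The table gives power by the normal approximation.

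| SD used | 70:70 | 100:70 | 113:57 |
|---|---|---|---|
| Change score, 4.49 | 0.83 | 0.88 | 0.85 |
| ANCOVA, 4.16 | 0.88 | 0.92 | 0.90 |
| Raw, 6 | 0.58 | 0.65 | 0.62 |

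Whichever SD is used, 113:57 lies above the 70:70 on which the plan's power rests and slightly below 100:70.

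**4. Could blocks of 3 still average 100:70?** The target share is 100/170 = 0.588. If a fraction x of blocks is 2:1 and the rest 1:2, then x × 2/3 + (1 − x) × 1/3 = 0.588, so x = 0.765. A list with about 76% of one kind and 24% of the other would average the target. The article describes no such list.

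**The case against.** The article is condensed and gives no within-block ratio, so the 2:1 is inferred. A fuller protocol might specify a mixed list, and step 4 shows that one is possible. This stands as a limit on certainty: blocks of 3 do not strictly rule out 100:70. But the article states both the block size and the arm sizes and presents one as the means to the other, and nothing in it suggests alternating compositions.

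A second defence is that 100 and 70 refer to patients with complete data, so the randomised split could differ. The only post-consent loss allowed for is 1% dead at t3, which cannot turn 113:57 into 100:70.

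The strongest objection concerns consequence, and it stands in full. A reader might infer that every sample-size statement depends on the 100/70 pair, or that the trial becomes underpowered. The documents do not support either. Three of the four questions use one arm of about 100, the fourth uses 70 per group, and the pair enters only through the concluding sentence and its sum. A reader might also infer that recruitment must rise until usual care reaches 70: at 2:1 that means 210 randomised, or 210 / (0.70 × 0.99) = 303.03, hence 304 approached. That treats 70 as a minimum whatever the size of the other arm. In the plan it is the group size of an equal-allocation calculation, and 57 against 113 gives more power than 70 against 70. Even closing recruitment at 100 decision-aid and about 50 usual-care patients gives change-score power of 0.80 to 0.81, essentially the stated value.

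**Conclusion.** The inconsistency is real: on the natural reading, the stated scheme yields about 113:57 at 170 patients, while the abstract, the Randomization section and the Sample size calculation state 100:70. Usual care is about 13 below its stated size, and chance imbalance from unfinished blocks does not close the gap. This rests on one assumption, that every block has the same 2:1 composition in favour of the decision aid.

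No stated power or precision is lost. Question 3 stays at about 0.85 on the method that approximately reproduces the plan's 0.81, and questions 1a, 1b and 2 gain slightly from the larger intervention arm. The comparison is not biased by the ratio. The point is a correction of numbers that should agree, cheap and worth making, but less than a must-fix defect.

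**What to change.** State the within-block allocation ratio in the Randomization section, then make the numbers agree in one of two ways.

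- **Keep 2:1.** Restate the arms as about 113 and 57 in the abstract, the Randomization section and the conclusion of the Sample size calculation, and give the question 3 power for those sizes, naming the SD used (about 0.85 by change score). This costs a few words and figures, and is the practical route once any envelope has been opened.
- **Change the list, only if no envelope has been used.** Generate it at a ratio near the target. At 3:2, for example, 170 patients give an expected 170 × 3/5 = 102 and 170 × 2/5 = 68, with change-score power of 0.88. Usual care would then average slightly under 70: with blocks of 5 and 10 over 33 equally likely sequences, the simulated mean was 68.0 (SD 3.7) and the chance of at least 70 was 0.34. The stated sizes should therefore be given as approximate. The cost is a new computer list and new envelopes.

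If a mix of 2:1 and 1:2 blocks was in fact intended, saying so with the proportions would settle the point. In every case the total of 170 and the 246 approached can stay, and no extra patients are needed.

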### Development of the decision aids

Decision aids on second-line treatment options for patients with advanced colorectal, breast, and ovarian cancer are developed. In this decision aid, the two treatment options are explained. Next, an overview of the potential risks and benefits of the two treatment options is presented. The information on risks and benefits is obtained from systematic reviews of the literature for each tumour type. Risk information includes the occurrence of serious adverse events, which are defined as grade 3 or 4 according to the Common Terminology Criteria for Adverse Events v3.0 (CTCAE) and are presented as adverse events that can be life threatening, can result in a hospital admission or prolongation of existing hospitalization, or can lead to a persistent or significant disability/incapacity. Tumour response is defined according to WHO or RECIST criteria and classified into overall response (complete or partial response), stable disease, and progressive disease. For both serious adverse events and tumour response, the probability that outcomes occur is presented in frequencies (n of 100 patients) and by means of pie charts, using a mixed frame, e.g. '22 out of 100 patients will experience severe diarrhoea, 78 out of 100 patients will not experience severe diarrhoea'. Information on survival is presented in the format of median survival.

### Interview

The decision aid is delivered by a nurse or by the researcher. First, the two treatment options are explained. Then, to familiarize patients with the general issue of trade-offs between benefits and risks, an example of a risky two-attribute non-cancer related choice is presented. After this example, the interviewer explains the first item of the decision aid regarding serious adverse events. This explanation includes the definition of a serious adverse event and gives the patient insight in the type of information that can be expected. Next, the patient is asked whether or not the information on serious adverse events is desired. The same procedure is followed for the other items on tumour response and survival. At the end of the interview, the patient can take home a brochure with information, tailored to the information desire of the patient. The interviewer fills in a questionnaire to register information desire and to provide a short evaluation of the interview.

### Outcome measures

Table 1 shows an overview of all outcome measures and the moment of measurement.

**Table 1 T1:** Outcome measures

Subject		Questionnaire	Inclusion	T1	Disease progression	Interview	T2	T3
**Sociodemographic characteristics**				x				
**Previous chemotherapy**				x				

**OUTCOME MEASURES & PREDICTORS OF INFORMATION DESIRE**								

**Well-being**	General Health			x			x	x
	Anxiety & Depression	Hospital Anxiety and Depression Scale		x			x	x
	Cancer Worries	Adapted Lerman's Cancer Worry Scale		x			x	x
	Health-related quality of life	EORTC QLQ-C15 PAL		x			x	x

**Coping**	Helpless/Hopeless, Avoidance, Fighting Spirit	Mental Adjustment to Cancer Scale		x			x	x
	Decision Styles	Michigan Assessment of Decision Style		x				
	Participation Preferences	Problem-Solving Decision-Making Scale		x				
	Perceived participation	Problem-Solving Decision-Making Scale					x	x
	Perceived involvement	Whelan					x	x
	Death avoidance	Death Avoidance Scale		x				

**Information**	Preference for information			x				
	Amount of information			x			x	x
	Information from oncologist						x	
	Undesired information						x	
	Information desire					x		
	Satisfaction with quality of information						x	x
	Balanced presentation of information						x	
	Evaluation of information						x	x
	Numeracy	Subjective Numeracy Scale		x				

**Knowledge**	General subjective knowledge			x				
	Treatment subjective knowledge						x	
	Objective knowledge						x	
	Subjective risk						x	
	Objective risk						x	

**Decision**	Decision satisfaction-uncertainty	Decision evaluation scale					x	x
	Decision control	Decision evaluation scale					x	x
	Weighing pros and cons	Decision evaluation scale					x	x
	Treatment choice					x	x	
	Strength of treatment preference					x	x	

**Treatment attitudes**	Valuations						x	x
	Treatment satisfaction							x
	Preferences for Quality/Quantity of Life	QQ Questionnaire		x				

**PHYSICIAN'S QUESTIONS**								

**Medical history**	Tumour and treatment characteristics		x					
**Substitute judgment**	Substitute judgment of information desire		x					
**Prognosis**	Estimate of survival				x			

#### Sociodemographic variables and medical history

Self-report data are collected at t1 on demographic variables (age, marital status, having (grand)children, being religious, working status, and education) and on previous chemotherapy, including experienced benefits and adverse events, and time since last chemotherapy. Tumour and treatment characteristics such as primary tumour site, previous chemotherapy, and time since diagnosis are filled in on the inclusion form by the medical oncologist. At the moment of disease progression, the medical oncologist is asked to estimate patient survival. Answer possibilities are 3-6 months, 6-9 months, 9-12 months, and more than 12 months.

#### Well-being

Patients rate their general health in the previous week on an 11-point rating scale (0-10). Anxiety and depression are assessed with the Hospital Anxiety and Depression Scale (HADS) [17]. Cancer worries are rated with three questions, adapted from Lerman *et al*. [18] and Stefanek *et al*. [19]: 'Did you think of cancer last week?', 'Did these thoughts affect your mood?', and 'Did these thoughts affect your daily activities?'. Health-related quality of life is assessed by means of the EORTC QLQ-C15 PAL quality of life questionnaire for cancer patients in palliative care [20].

#### Coping

Coping with cancer is assessed with the Mental Adjustment to Cancer scale [21]. Three coping strategies are assessed: helplessness/hopelessness, avoidance, and fighting spirit. The patient's decision style is assessed with The Michigan Assessment of Decision Style (MADS) [22]. The MADS covers (1) avoidance (four items, e.g. 'I prefer not knowing the possibility that unexpected things could happen to me'); (2) deferring responsibility (three items, e.g. 'I would follow the recommendations of my physician'); (3) information seeking (four items, e.g. 'I would spend as much time as I could gathering information'); and (4) deliberation (five items, e.g. 'I would carefully consider the risks of each option as I was making a choice'). The general participation preference at baseline is measured with the two decision-making items from the Problem-Solving Decision-Making Scale [23]. The questions are as follows: 'When the risks and benefits of the treatment options are known to you, (1) who decides how acceptable those risks and benefits are for you and (2) who decides what treatment should be selected?'. Answers range from 'only the physician' to 'only me'. Perceived participation is assessed by the same questions in past tense, after the decision is made. Perceived involvement is measured by asking patients whether they felt they were offered a choice between BSC plus chemotherapy and BSC alone [24]. In addition, patients are asked whether their opinion regarding the treatment mattered. Both questions use a yes/no response. Death avoidance will be measured by means of the Death Avoidance Scale, which was adapted by Kaplowitz *et al*. 2002 [25] from the original Death Acceptance Scale developed by Klug and Sinha (1987) [26]. The two items are as follows: 'I avoid discussing death when the occasion presents itself' and 'I make a conscious effort to avoid dwelling on thoughts of death', and are measured on a 5-point scale (1 = strongly disagree, 5 = strongly agree).

#### Information

The preferred amount of information is measured on a 11-point scale ranging from 0 (I want to know nothing about the illness and its treatment) to 10 (I want to know everything there is to know about the illness and its treatment) [8]. The amount of information received about the treatment choice is measured on a 7-point scale ranging from 1 (I received way too little information), 4 (I received exactly enough information), to 7 (I received way too much information). Information received during the consultation with the oncologist, regarding adverse events, tumour response, and survival, is assessed using a yes/no response. Whether patients received any undesired information is asked with a question using a yes/no response. The key variable information desire is described under 'Interview' above. Satisfaction with the quality of information is asked with three questions related to information on adverse events, tumour response, and survival. Responses are on a 6-point scale ranging from 1 (not satisfied) to 6 (very much satisfied). The balanced presentation of information is evaluated on a 5-point scale from 1 (clearly in favour of chemotherapy plus BSC), 3 (balanced), to 5 (clearly in favour of BSC alone). Six questions are asked about unpleasant, shocking, frightening, and threatening experiences with the information received, measured on a 5-point scale from 1 (no negative experience) to 5 (very negative experience). Numeracy, i.e. the ability to handle basic probability concepts, needed for the interpretation of risk information, is measured by the Subjective Numeracy Scale (SNS) [27].

#### Knowledge

Patients rate their own knowledge (subjective knowledge) on cancer treatments with a single question on a 10-point scale ranging from 1 (very bad) to 10 (excellent). Two questions are asked to assess the subjective knowledge with respect to risks and benefits of treatment options on a 10-point scale. Objective knowledge will be measured with a questionnaire containing five statements related to the two options BSC plus chemotherapy and BSC alone. These statements have to be judged as right or wrong. Subjective risk perception is measured by three questions on the chance of experiencing a serious adverse event from 1 (very high) to 5 (very low), the chance that stable disease or a response will be achieved by BSC plus chemotherapy, as opposed to BSC alone from 1 (much higher) to 7 (much lower), and the chance of experiencing pain on treatment with BSC plus chemotherapy, as opposed to BSC alone from 1 (much higher) to 7 (much lower). Objective risk perception is asked for the chance of experiencing severe diarrhoea, and the chance of achieving a response. Patients are asked to give a risk estimate for these two outcomes in a range from 0% to 100%.

#### Decision

Satisfaction and uncertainty regarding the choice between BSC plus chemotherapy and BSC alone are assessed using five items [28], e.g. 'I find it hard to make this choice', 'I am satisfied with my decision', measured on a 5-point scale (1 = strongly disagree, 5 = strongly agree). Patients are also asked about their feeling of control regarding this treatment choice using five items [28], e.g. 'This decision is made without me', 'I feel pressure from others in making this choice', measured on a 5-point scale (1 = strongly disagree, 5 = strongly agree). Weighing of pros and cons of the treatment options was asked with a single question 'I weighed the pros and cons', on a 5-point scale (1 = strongly disagree, 5 = strongly agree). Treatment choice is collected by asking which treatment patients prefer. Response options are: BSC plus chemotherapy, BSC alone, don't know. Strength of treatment preference (for one or the other option) is asked on a 4-point Likert scale ranging from 1 (weak preference) to 4 (very strong preference).

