## Background

Good clinical practice encompasses optimal providing of information to patients. However, as yet the debate about the desirability of informing patients with cancer and thereby involving them in their own care process has not been resolved. On the one hand, it has been shown that patients with more severe disease may become emotionally unstable and tend to leave decision making to their physician [1-3]. Furthermore, patients with cancer may sometimes deny their illness [4]. In short, patients may wish 'not to know'. All these factors hamper the uptake of information. It is conceivable that additional stress could be inflicted upon patients by involving them in decisions which are complex, emotionally hot, with high personal stakes and have to be taken under time pressure. These circumstances are unfavourable for rational decision making [5]. Taken these arguments together, the positive effects of informing cancer patients with relevant information for treatment decision making can be questioned.

On the other hand, cancer patients desire to be informed about risks and prognosis. A systematic review of Gaston *et al*. (2005) [6] showed that almost all cancer patients wish to be fully informed, regardless of the stage of their disease. Studies using the questionnaire that was developed by Cassileth *et al*. 1980 [7] showed that 83%-92% of advanced cancer patients wanted as much information as possible, whether good or bad [7-10]. Hagerty *et al*. 2004 [11] more specifically explored the desire for prognostic information and showed that over 80% of advanced cancer patients wanted to know the longest time to live with treatment, 5-year survival rates, and average survival. Unlike the aforementioned studies that probed preferences, Elit *et al*. [12] actually delivered information to patients with advanced gynaecological cancer. A decision instrument was used to present information on two chemotherapeutic treatment options and their potential risks and benefits. Survival information was desired by and provided to 92% of the women. However, these patients were asked to make a hypothetical decision, since the treatment choice would not actually be carried out. In the present study, we will assess patients' information desire by offering information in a decision aid at the point of decision making. The treatment choice of patients will actually be carried out.

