In conclusion, we aim to settle the debate on the desirability of informing patients with cancer by developing a decision aid to assess the amount of information desired by patients with advanced cancer at the point of decision making. The study population will consist of patients with advanced colorectal, breast, or ovarian cancer who are treated with first-line chemotherapy and upon disease progression will face the choice between two equivalent treatment options. These patients can decide to have second-line chemotherapy in combination with BSC, or they can refrain from further chemotherapy and opt for BSC alone. Second-line chemotherapy may induce tumour response and prolong survival, but also entails a risk of serious adverse events. Our research questions are: 1a) Do these patients want to be informed about the treatment options, and specifically about their prognosis? 1b) Which factors determine whether or not these patients want to be informed? 2) Can the medical oncologist judge whether or not the patient wants the risk information? 3) What is the effect of the decision aid on patient outcomes (well-being, information and decision related outcomes, treatment choice) compared to usual care?

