### Procedure

The medical oncologist, or a nurse who first consulted the medical oncologist, will inform eligible patients in a general way that this study focuses on 'how to involve the opinion of patients in the treatment'. Next, he or she will ask whether the researcher can contact the patient by phone about this study. The oncologist or nurse is instructed not to discuss that survival information can be provided in the study, in order not to lose patients not desiring such information. After the visit of the patient, the oncologist fills in the medical history on the inclusion form. He or she also makes a judgment whether or not the patient will desire information about adverse events, tumour response, and median survival that will be offered in the interview (research question 2). In the phone call, patients are explained that data are collected by means of three questionnaires and possibly an interview. All patients who agree to participate will provide written informed consent.

Patients will be sent a baseline questionnaire (t1) to collect sociodemographic data, well-being measures, and measures that predict information desire. When tumour progression is diagnosed, second-line chemotherapy will be offered by the oncologist and randomization will be performed. Patients in the usual care group will receive information about the treatment choice from their oncologist. In the intervention group, patients will receive the same information, and will in addition be offered information in an interview using a decision aid. At the moment of disease progression, the medical oncologist is asked to estimate patient survival, because this is expected to be associated with the patient's information desire.

To evaluate the effect of the decision aid, two follow-up questionnaires will be sent to the patients, one week (t2) and eight weeks (t3) after the treatment choice, before the first evaluation of chemotherapy. Figure 1 displays the complete procedure.

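### Treatment choice under question 3 is defined as a stated preference, and no listed measure records the option actually taken

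*Protocol article*

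**What the plan says.** The research questions at the end of the Background ask: "What is the effect of the decision aid on patient outcomes (well-being, information and decision related outcomes, treatment choice) compared to usual care". Treatment choice is thus an outcome of the randomized comparison. Earlier in the Background the trial is set apart from a study in which women with gynaecological cancer made only a hypothetical decision; here, "The treatment choice of patients will actually be carried out".

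The Decision subsection then states how the outcome is obtained: "Treatment choice is collected by asking which treatment patients prefer. Response options are: BSC plus chemotherapy, BSC alone, don't know".

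Table 1 is introduced with "Table 1 shows an overview of all outcome measures and the moment of measurement". Its row "Treatment choice" is marked at Interview and at T2, and nowhere else. Under Procedure, the interview belongs to the intervention group only, while the two follow-up questionnaires go to patients without restriction by arm, "one week (t2) and eight weeks (t3) after the treatment choice, before the first evaluation of chemotherapy".

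**The concern.** A preference and the option taken are different variables. The protocol itself allows for a gap between them: the participation items let the patient answer that the physician alone decided, and the decision-control items include one on a decision made without the patient. At T2 the choice is a week old, yet the item still asks for a preference and accepts a don't-know answer. A patient whose treatment is settled could therefore be recorded as undecided, or under the option not taken.

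At stake is the article's own claimed advance. The trial studies a choice that is acted on, but none of its listed outcomes shows how patients acted. A result on treatment choice would describe what responders said they preferred, and readers could easily take it for uptake of second-line chemotherapy.

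**Working it through.** This is mainly a check of definitions, so the places are set side by side.

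1. **Outcome named.** Research question 3: treatment choice, decision aid against usual care.
2. **Outcome measured.** Decision subsection: the preferred treatment, with three response options, one of them don't know.
3. **When.** Table 1: Interview and T2. The interview takes place in one arm only, so T2 is the single time point common to both arms.
4. **Could another item supply the option taken?**
   - Physician's questions in Table 1: medical history and substitute judgment at inclusion, and a survival estimate at progression. None is about the treatment chosen.
   - Treatment attitudes: valuations of both options at T2 and T3, and at T3 satisfaction with the treatment received. The satisfaction item presupposes a treatment but does not ask which one.
   - Strength of preference: same time points as the preference item, and again a preference.
5. **Result.** No listed measure identifies the option taken in either arm. The available comparison is preference at T2, in those who return the form and answer the item.

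**The plan's own figures.** No power or sample size is given for treatment choice. The figures given concern other matters and can be reproduced:
- HADS anxiety, change-score SD = 6 × √(2 × (1 − 0.72)) = 4.49. With a difference of 2.2, 70 per group and two-sided α = 0.05 (sidedness assumed), power is 0.826 by the normal approximation, close to the stated 0.81.
- Patients approached: 170 / 0.70 / 0.99 = 245.3, hence 246.

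Neither figure depends on how treatment choice is measured.

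**Illustration of incompleteness, on assumed rates.** Let a share m of each arm have no usable T2 answer, and let p be the share of answerers in an arm preferring one option. If preference equals action in those who answer, the true share in that arm lies between (1 − m)p and (1 − m)p + m, a band of width m. For the difference between two arms the worst-case band is 2m wide:
- m = 5%: 10 points
- m = 10%: 20 points (7 of 70 and 10 of 100 patients without an answer)
- m = 20%: 40 points

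These are limits for extreme cases, not expected bias. Chart data on every randomized patient would remove this band.

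**The case against.** The strongest reply is that T2 does provide a like-for-like comparison. It goes to both arms at the same interval after the choice, and the Statistical Analysis section provides a chi-square test for categorical variables at a single time point. This stands: the treatment-choice part of question 3 can be addressed for stated preference among responders.

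A second reply is that the article condenses a fuller protocol. Staff must learn when a choice is made in order to time T2 and T3, so the option taken may well be in the hospital records. That shows the information is within reach. It does not fully answer the point, because the article presents Table 1 as covering all outcome measures and positively defines treatment choice as a preference. This is a definition that does not match the named outcome, rather than a detail left out.

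Third, nothing in the article shows that preference one week after the choice departs materially from the option taken, or that don't know would be common at that point. This also stands. The gap is possible and its size is unknown.

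Two stronger readings are tempting and are not supported:
- A reader might infer that missingness differs by arm because interview answers could replace absent T2 answers in the decision-aid arm. No section says they will be used that way, and having a second measurement in one arm does not bias a comparison made at T2. Nor does the article say who would fail to return T2.
- A reader might set an assumed one-arm uncertainty band beside a detectable difference between arms and conclude that the comparison is uninformative. Those are different quantities, the rates are assumed, and the outcome was never powered.

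**Conclusion.** The point holds in a limited form. The outcome named in question 3 is treatment choice, the outcome measured is stated preference, and no listed item records the option taken. The arms can be compared on preference among T2 responders, but not on real choices in all randomized patients.

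This conclusion follows from the text and needs no assumed rate. How far a preference-based result would differ from one based on actual choices cannot be determined from the document; the bands shown above illustrate only the missing-answer part and depend on the assumed m. It would go too far to say that question 3 cannot be answered. Its main outcome is HADS anxiety, and that analysis, the primary question on information desire and the sample size all stand. The point is a worthwhile, low-cost improvement to a secondary outcome.

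**What to change.** - For every randomized patient in both arms, record from the medical record which option was actually taken (second-line chemotherapy plus BSC started, or BSC alone), with its date. Use this as the treatment-choice outcome for question 3.
- State beforehand how a patient is coded who decides for chemotherapy but does not start it, so that the variable has one meaning in both arms.
- Rename the present item treatment preference. Keep it as a separate secondary outcome, compared between arms at T2 only.
- Use the interview preference descriptively within the decision-aid arm.
- Add the corresponding row to Table 1 and amend the Decision subsection.

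The cost is one extra chart field with a date per randomized patient (170 as planned) and a few sentences of text. It needs no new visit, adds no patient burden and leaves the sample size unchanged.
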